## Abstract

**Background:**

Tinnitus is a particularly common condition and can have debilitating psychological consequences for certain people. Although several interventions have been helpful in teaching individuals to better cope with tinnitus, no cure exists at present. Neurofeedback is an emerging treatment modality in tinnitus. Previous studies, utilising an alpha/delta training protocol, have shown promise. However, they were characterised by small sample sizes and a lack of neurofeedback control conditions. Therefore, the aim of this study is to investigate whether an alpha/delta neurofeedback training protocol, compared to beta/theta neurofeedback or a diary control group, is effective in reducing not only the tinnitus sound perception but also the psychological symptoms associated with the condition.

**Methods:**

The study is designed as a three-armed randomised controlled trial. Participants are randomly assigned to a) an established neurofeedback protocol for tinnitus (alpha/delta training), b) an active control group (beta/theta training) or c) a diary control group. In the 4-week intervention period, participants in both neurofeedback groups undergo 10 sessions, whereas participants in the diary control group complete a bi-weekly diary. The primary outcomes are between group differences in tinnitus sound perception change, as measured with the Tinnitus Magnitude Index (TMI), and changes in tinnitus distress, measured with the Tinnitus Handicap Inventory (THI), 4 weeks after the start of the intervention. Secondary outcome measures include changes in tinnitus distress, sleep quality, depressive symptoms and whether neurofeedback leads to specific power changes in the trained frequency bands.

**Discussion:**

This is the first randomised controlled trial examining the efficacy of an alpha/delta neurofeedback training protocol in reducing tinnitus sound perception and the distress associated with the condition. Compared to former studies, the present study is designed to assess both the specificity of an alpha/delta neurofeedback training protocol by including an active comparator and beta/theta neurofeedback training, in addition to controlling for placebo effects by the inclusion of a diary control group. This study aims to contribute to an understanding of the influences of both specific and non-specific effects in neurofeedback treatment for tinnitus.

**Trial registration:**

ClinicalTrials.gov: NCT03550430. Registered on 27 May 2018.

## Introduction

Tinnitus, the perception of sound in the absence of external acoustic stimuli [1], is a rather common condition. However, getting a precise prevalence estimate poses a challenge. This is largely due to the heterogeneity of tinnitus definitions in research [2]. Nevertheless, prevailing research points to an estimated 10 to 20% of the general population experiencing tinnitus [2, 3]. Although most manage to live well with—and tolerate—the condition, for 2 to 3% of the population, the condition is so severe that it seriously interferes with their quality of life [2, 4]. Feelings of despair, hopelessness, anxiety and depression are commonly reported by distressed tinnitus patients, as are concentration difficulties and insomnia [5, 6].

Prior to advances in neuroscience, models in tinnitus emphasised peripheral auditory structures as the locus of tinnitus generation (e.g., [7]). Although tinnitus is likely precipitated by damage to the cochlea and/or auditory structures, current theories and models hold that it is generated and perpetuated in the brain [8] as basic assumptions. In individuals with tinnitus, spontaneous resting-state brain activity has been found to differ from that of healthy controls. For the interested reader, [9, 10] provide very readable, recent and updated accounts of neurophysiological models of tinnitus. Given the focus of the present study, the findings from neuroimaging studies, such as those outlined in, for example, [9], are important and have led to the development of several experimental neuromodulation techniques, ultimately seeking to redress the imbalances in aberrant neuronal activity. One such technique, which in the past decade has spawned considerable research activity, is neurofeedback [10]; generally, the goal of neurofeedback is the promotion of healthier brain wave patterns (e.g., [11]). Normally, brain wave activity occurs outside of conscious awareness, but by presenting it in an audio- and or visual format to a neurofeedback trainee, he/she has the possibility of influencing it, ultimately achieving more optimal brain functioning (11).

In the past decade, one finding of differences in resting state brain activity between individuals with tinnitus and healthy controls has given rise to significant experimental activity in the field of neurofeedback. In individuals with tinnitus, compared to healthy controls, reduced alpha and increased delta brain wave activities over temporal regions were observed [12]. This led to the development of neurofeedback training protocols aimed at reversing this abnormal brain activity pattern in individuals with tinnitus [13]. Using an alpha/delta ratio (ADR) training protocol, with the goal of simultaneously uptraining alpha- and down-training delta activity, three studies have arrived at similar conclusions regarding the effectiveness of neurofeedback: participants in all studies report improvement in their overall psychological well-being upon completion of neurofeedback training [9, 13, 14]. Moreover, the loudness perception also seemed to be influenced by the training when rated immediately upon completion of the intervention [13, 14]. Over time, however, this effect appeared to be less robust compared to the psychological benefits of neurofeedback and returned somewhat to baseline [9]. In summary, the results of ADR neurofeedback training on the distressing aspects of tinnitus are encouraging. Nevertheless, in these studies, as in neurofeedback studies in general [15], the influence of non-specific factors are largely ignored or otherwise not accompanied with controls. In neurofeedback, this neglect is particularly critical, as factors such as expectancy, motivation, therapist interaction and demand characteristics are assumed to play a significant, if not decisive role [9, 15–17]. Some (e.g., [16]) even consider these effects to be the healing mechanisms in neurofeedback.

One way to address this concern is to demonstrate a correlation between the self-regulation of brain activity and behavioural outcomes, i.e., outcome specificity [18]. In all of the studies assessing the effectiveness of the ADR training protocol on tinnitus, outcome specificity was reported, but with mixed conclusions. Dohrmann and colleagues [13] identified a significant correlation between changes in the ADR and tinnitus intensity reduction. This association was not significant for the correlation between the ADR and tinnitus distress. Conversely, Crocetti and colleagues [14] found changes in the ADR to be significantly associated with improvement in well-being, whereas for intensity perception, no association was observed. Lastly, Güntensperger and colleagues [9] reported outcome specificity to be mainly associated with increments in alpha frequency band activity. Overall, taking them at face value, the three studies demonstrate some elements of outcome specificity, which in turn speaks in favour of the reduced influence of non-specific effects on the outcome. However, ruling that non-specific effects were indeed the agents of change in these studies is premature when taking into consideration that 1) non-specific effects can lead to changes in brain activity [19], and more importantly, that 2) alpha frequency band activity is particularly susceptible to the influence of non-specific effects [15]. Hence, when changes in brain wave frequency bands, particularly the alpha band, are observed in neurofeedback studies, this treatment effect may wrongly be attributed to a specific effect of the treatment, when in fact non-specific effects may equally account for it.

The goal of the present study is thus to advance our knowledge of the influence of specific versus non-specific effects in ADR neurofeedback training for tinnitus. To ensure comparability with previous studies (i.e., [9, 13, 14]), a number of parameters are identical (see Methods section). However, two control conditions have been added to the study to explore whether the healing mechanisms of neurofeedback for tinnitus are indeed specific to ADR neurofeedback or whether other effects can account for the improvement in tinnitus sufferers’ well-being. The first of these control conditions is a beta/theta ratio (BTR) neurofeedback intervention. The decision to include this is informed by researchers (e.g., [15]) who have suggested that the only way to assess the efficacy of a particular neurofeedback training protocol (in this case, ADR) is to subtract the effects of an identical protocol while barring the neural targets (in this case, BTR). Although no neurofeedback study for tinnitus has used the specific BTR training protocol to date, this protocol has been used in studies aimed at enhancing attention [20], both in clinical (e.g., [18, 21, 22]) and in healthy (e.g., [20]) populations. Because all factors other than the trained frequency bands are identical between ADR and BTR, we assumed this control condition to be the most suitable to effectively control for non-specific participant factors in the present study. The diary control intervention comprises the third arm of the study. In this section, components are included that are intended to promote or enhance non-specific effects, such as expectancy, motivation, demand characteristics and the therapeutic alliance. By subtracting the influence of these from those of the neurofeedback groups, an estimate of the magnitude of non-specific effects in neurofeedback can be gauged.

Our hypotheses are based on the following arguments. First, ADR neurofeedback training was developed specifically to restore an imbalance in excitatory/inhibitory neuronal activity in the auditory cortex in individuals with tinnitus [13] and, therefore, should be more efficacious than BTR neurofeedback. Second, the ADR protocol has been used with success to reduce distress and/or intensity in three prior studies [9, 13, 14]. Third, given the added influence of non-specific effects in neurofeedback, participants in the ADR and BTR groups will have greater expectations of treatment outcomes than participants in the diary control condition. Based on these observations, we hypothesise the following:
Participants undergoing ADR neurofeedback training will report significantly stronger reductions in tinnitus distress and intensity from pre- to post-treatment compared to participants undergoing BTR neurofeedback.Participants in both the ADR and BTR neurofeedback interventions will improve more significantly in measures of tinnitus distress and intrusiveness from pre- to post-treatment Methods/Design

### Study Design

The study, a three-armed, randomised controlled trial, will be conducted at Philipps University in Marburg, Germany. The study has been approved by the respective ethics committees of the Department of Psychology and the Department of Medicine at Philipps University with registration numbers 2018-4 k (Additional file 2) and 162/18 (Additional file 3), respectively. Furthermore, the trial is registered with clinicaltrials.gov (ClinicalTrials.gov Identifier: NCT03550430).

Sample size calculations were based on a repeated-measures multivariate analysis of variance (MANOVA) and conducted with G*Power 3.1.9.2 [23].. The total sample size needed to detect a medium assessment-by-treatment interaction effect (*f* = 0.25, *Beta* = 0.80, *Alpha* = .05, Groups = 3, measurements = 3) is 98. However, to compensate for an estimated dropout rate of 20% during treatment, the aim is to recruit 120 participants, i.e., 40 participants per group. Post-hoc analyses are carried out between ADR vs. BTR, ADR vs. diary control and BTR vs. diary control.

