### Statistical analysis

Data will be analysed primarily in the intention-to-treat (mITT) population. Supportive analyses are planned in the per-protocol (PP) population. mITT comprises all randomised patients, while PP analysis assesses mITT patients who show no change in their status during the trial period that violates the criteria for their inclusion/exclusion (for example, the data from someone seeking another type of treatment for their tinnitus during the trial period is excluded from further analyses).In addition, data from participants who deviate significantly from the visit schedule are excluded from analyses, and data from participants who show poor compliance during feedback sessions are excluded (e.g., showing sleepiness or lack of focus and orientation to the task). For all outcome measures, we will probe the longitudinal course across all assessments using a linear mixed model for repeated measures (MMRM, see [61]). The MMRM model includes fixed effects for group (ADR vs. TBR vs. diary control), time and group-by-time interaction, as well as a random intercept for subject specific effects using maximum likelihood estimation, adding sex, age, baseline tinnitus severity scores and patients’ expectations as covariates. The error variance-covariance matrices for the repeated factor will be specified in accordance with the data. The pattern of missing data is assumed to be random.

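### Minor: 120 recruits less 20% dropout leaves 96, two short of the 98 required, so the sample-size sentence needs restating (about 79% power if dropouts give no data)

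*Protocol article*

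**What the plan says.** The Study Design section names the sizing method: "Sample size calculations were based on a repeated-measures multivariate analysis of variance (MANOVA) and conducted with G*Power 3.1.9.2". The target is to "detect a medium assessment-by-treatment interaction effect (*f* = 0.25", with 0.80 entered under the label Beta and alpha at .05, and the result is given as "Groups = 3, measurements = 3) is 98". The text then adjusts for attrition: "to compensate for an estimated dropout rate of 20% during treatment, the aim is to recruit 120 participants", which it splits into 40 per group. It does not show how 120 was obtained or how many completers are expected.

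The Statistical analysis section sets the primary population and model. There, "mITT comprises all randomised patients", and the outcomes are analysed with a mixed model for repeated measures fitted by maximum likelihood, with missing data assumed to be random.

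**The concern.** Three linked figures (98 needed, 20% lost, 120 recruited) cannot all hold. If 120 are recruited and a fifth are lost, fewer than 98 remain, so the inflation does not fully do what the sentence claims. Sample size and power are among the first figures a reader checks, and this check takes one line. The same sentence labels 0.80 as beta. Beta conventionally denotes the type II error rate, so taken literally the label would mean 20% power.

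**Working it through.** **Inputs, all from Study Design:** repeated-measures MANOVA, assessment-by-treatment interaction; f = 0.25; alpha = 0.05; k = 3 groups; m = 3 measurements; target 0.80, read as power; dropout 20%; recruitment 120 (40 per group).

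**Step 1: reproduce 98.** For the within-between interaction (Pillai-type test, f read as G*Power's f(V)):
- p = m − 1 = 2, q = k − 1 = 2, s = min(p, q) = 2
- df1 = p × q = 4
- df2 = s(N − k − p + s) = 2(N − 3)
- noncentrality λ = s × N × f² = 2 × N × 0.0625 = 0.125 N
- power = P(noncentral F(df1, df2, λ) > F critical at 0.95)

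| N | df2 | λ | Power |
|---|---|---|---|
| 96 | 186 | 12.000 | 0.7909 |
| 97 | 188 | 12.125 | 0.7957 |
| 98 | 190 | 12.250 | 0.8005 |
| 120 | 234 | 15.000 | 0.8842 |

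The smallest N with power of at least 0.80 is 98, an exact match to the article. The match also settles two readings: f is on the f(V) scale, and 0.80 is power. For comparison, a univariate repeated-measures ANOVA with an assumed correlation of 0.5 would need only 35, so that option was not the one used.

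**Step 2: check the inflation.**
- Completers at 20% dropout: 120 × 0.80 = 96, two below 98.
- Exact inflation: 98 / (1 − 0.20) = 122.5, so 123 (41 per arm). The stated 120 is 3 short, or 3 / 120 = 2.5%.
- Multiplying up instead: 98 × 1.20 = 117.6, so 118. This does not give 120 either.
- Largest dropout that still leaves 98 of 120: 1 − 98/120 = 18.3%.

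**Step 3: effect on power.** 0.8005 − 0.7909 = 0.0096, about one percentage point, if dropouts contribute nothing. If all 120 contributed complete data, power on the same basis would be 0.884.

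**The case against.** The strongest reply is that the gap is at rounding level. The 20% is described as an estimate, 120 covers up to 18.3%, and a difference of 1.7 points in a round assumption has no practical effect on the trial. That stands as to size. It does not make the sentence correct, because the sentence claims compensation for 20%.

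A reader might go further and infer that the trial will not deliver its stated 80% power. The document does not support that, for three reasons:
- The primary analysis is not restricted to completers. It takes all randomised participants into a maximum-likelihood mixed model. The Procedure/trial protocol section places a mid-point assessment two weeks into the four-week intervention, so some who drop out will have baseline and mid-point values. The Limitations section also stresses completion of outcome measures whatever a participant's status in the trial, so stopping treatment need not mean losing outcome data.
- The 0.791 belongs to the MANOVA used for sizing. The planned mixed model, with covariates, is a different analysis, and its exact power cannot be read from this calculation.
- 96 full contributors is the least favourable case under the 20% assumption, not the expected one.

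A reader might also object that 98 does not divide into three equal arms. That is no error: 98 is the minimum total from the power calculation, and the allocation target is 40 per arm. The beta label is a notational slip. Since 98 reproduces with power of 0.80, the intended meaning is clear and no number changes.

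**Conclusion.** The point holds as a minor inconsistency in the sample-size statement. Under the article's own 20% assumption, 120 recruits leave 96 completers against 98 required. Power on the sizing test is then about 79.1% instead of 80%, provided dropouts contribute no data. On the same f = 0.25 basis, partial data from dropouts would put power somewhere between about 79.1% and 88.4%, the upper end requiring full data from all 120. The conclusion rests on the f(V) reading of the effect size, which the exact match at 98 supports. It does not show an underpowered trial or a need to recruit more participants.

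**What to change.** Keep 120 (40 per group) and restate the sentence in one of two ways:
- recruiting 120 allows for about 18% dropout while retaining 98 participants; or
- with 20% dropout 96 complete, giving about 79% power on the stated MANOVA if dropouts contribute no data.

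In the same sentence, give 0.80 as power (1 − beta) in place of beta. The cost is one sentence, with no extra participants and no change to design or analysis. The stated dropout allowance or the stated power becomes slightly less favourable.

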### Inclusion and exclusion criteria

Participants are eligible for inclusion if they meet the following criteria:
Age + 18 yearsChronic, subjective tinnitus with a duration of ≥ 6 monthsAt least mild tinnitus distress, corresponding to a score of ≥ 18 on THI [24]Signed informed consent

The study’s exclusion criteria are as follows:
Objective tinnitus, either vascular or non-vascular in originAcute inflammatory disease of the ear/earsConductive hearing lossBlockage of the ear canal by, for example, cerumen, where removal is not desired by the individualAny current treatment for tinnitusSevere mental health issues (moderate/severe depression, bipolar disorder, psychosis)ADHDCurrent use of a psychotropic drug for a mental health conditionSubstance abusePrevious or current neurofeedback treatmentPrevious or current neurological conditions (e.g., a history of seizures, brain tumour, haemorrhage/stroke).

### Procedure/trial protocol

Recruitment for the trial is completed primarily through advertisements placed in local and regional media. In addition, a referral programme is established to entice ear-nose-throat physicians (ENTs) to forward participants to the study. Interested individuals can read more about the study on a dedicated website, where they also can register their interest in trial participation. Both the website and the questionnaires are provided via the Iterapi platform [25].

The enrolment period (t0, see Fig. 1) is a four-stage process. In the first stage, participants complete a battery of online screening questionnaires. These are principally designed to sort individuals into eligible and non-eligible categories, based on the inclusion/exclusion criteria. Prior to taking the screening questionnaires, participants will give informed consent for questionnaire completion only. For principally eligible individuals, the second stage in the screening process is a telephone interview. The purpose of this is to validate questionnaire responses and to assess their motivation to participate in such a trial. The third stage in t0 is a visit to the Department of Psychology. The first part of this visit provide participants with detailed information about the study, its procedures and how to complete baseline assessments, including primary and secondary outcome measures on the secure online platform. Following this, participants sign the informed consent form (see Additional file 4) and complete the State Anxiety Inventory online (STAI) [26]. Participants then complete two attention tests, the Attention Network Task (ANT) [27] and the Sustained Attention to Response Task (SART) [28], referred to in Fig. 1 as the cognitive assessment.

**Fig. 1 Fig1:**
[figure not shown]
Schedule of enrolment, interventions and assessments

The fourth and final stage in t0 is a standard audiological examination at the ENT-clinic at the University Hospital of Giessen and Marburg (UKGM). There are two main purposes for this visit: The first is to rule out possible non-subjective causes of tinnitus, and the second, to acquire audiometric data. At the clinic, participants first learn about the components of the audiological examination before signing the informed consent form (see Additional file 5). Subsequently, the audiological examination, in which the below information is acquired, takes place:
Standard Audiogram (to 20.000 Hz)TympanometryOtoacoustic emission (OAE)Tinnitus loudness discomfort levelTinnitus matching (loudness, pitch)

Participants who are included after the visit to the ENT clinic take the baseline assessment in the pre-allocation (t1) stage. Upon completion of this assessment, participants move to the allocation (t1) stage and are randomly assigned to one of three arms in the study: Group 1, which receives alpha/delta neurofeedback training; Group 2, which receives beta/theta neurofeedback; and Group 3, which is the diary control group.

The post-allocation (t2) intervention period lasts 4 weeks. Within this timeframe, ten neurofeedback training sessions are undertaken for the two neurofeedback groups, with a minimum of two and maximum of three sessions per week. For the diary control group, two face-to face visits to the department and two telephone calls are scheduled within the 4-week period. t2 mid-point assessments are completed 2 weeks after the start of the intervention. In the post-allocation (t3) stage, participants complete the endpoint assessment online prior to a visit to the Department of Psychology, where they complete the ANT and SART (referred to as cognitive assessment II in Fig. 1). t3 post-assessments are completed 4 weeks after the start of the intervention.

The t4 follow-up takes place 4 months after the start of the intervention. Here, participants in the neurofeedback groups complete assessments online before coming to the Department of Psychology for a booster neurofeedback session. The booster sessions serve the practical goal of probing the participants about their experiences with neurofeedback. Moreover, the visit is included to increase the likelihood of participant adherence to questionnaire completion. For diary control participants, t4 assessments are completed 4 months after the start of the intervention. As a token of appreciation, they then receive a copy of a self-help book on tinnitus [29].

